### Statistical method and analysis

Assessments of statistical procedures will be performed using IBM SPSS version 20 for Windows (SPSS Inc., Chicago, IL, USA). All variables will be reported using the descriptive statistic (mean, standard deviation). Shapiro-Wilk test will be used to assess the normality of data. Repeated measures ANOVA will be used to compare the means. If mean difference is significant, then the Bonferroni-adjusted post-hoc test will be calculated. The independent *t*-test will also be used for comparison between groups. Finally, the effect size will be calculated for the magnitude of the difference using the Cohen method. The significance level will be set at *p* < 0.05.

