### Study participants and eligibility criteria

The participants consist of 24 men with UCS aged 18 to 28 years. They will be recruited from the students of the University of Tehran, Iran, through advertisements on bulletin boards. They will be screened primarily by observation for three main factors related to UCS, including altered alignment, muscle activation, and movement patterns. Since the scapulae are the keystone in UCS, participants who have any abnormality in the position and rhythm of the scapula, as measured by the scapular dyskinesis test, will be recruited. In addition, they will be assessed for presenting any postural changes such as forward head (≥ 44°), round shoulder (≥ 49°), or excessive thoracic kyphosis (≥ 42°) as measured by photogrammetry and flexicurve, respectively [15]. Also, to ensure any change in muscle activation is related to postural changes, some confirmatory tests, including muscle length tests for upper trapezius and pectoral muscles as well as muscle strength tests for middle and lower trapezius and deep cervical flexor, will be used. Individuals will be excluded from the research process if they do extra physical activity and sports that may affect the outcomes of the research, have any visible malalignment in the pelvis and lower extremities, have a history of fracture, surgery, or joint diseases in the spine, shoulder and pelvis, have a rotation greater than 5° on the forward bending test because of scoliosis [15], or have a bodyweight outside the normal range (body mass index between 18 and 25) [23].

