#### Outcome measures

Upper trapezius activation (measured with surface electromyography) is the primary outcome measure. Secondary outcomes include electromyography measurements of middle and lower trapezius and serratus anterior muscles, scapular dyskinesis, forward head and shoulder angles, thoracic kyphosis angle, and neck flexion pattern.

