##### Scapular dyskinesis

The current recommendation for clinical assessment based on a prior consensus meeting is the use of the dynamic scapular dyskinesis test according to the procedure described by McClure et al. [35]. The position and motion of scapula are characterized by dyskinesis as a “yes” (presence of deviation or dysrhythmia/asymmetry bilaterally) or “no” (no presence). This method has been shown to be reliable among observers and has acceptable clinical utility [35, 36].

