##### Neck flexion pattern test

The participants will lie supine with knees bent. They will then be instructed to lift the head and look at their toes. Normal movement produces a smooth reversal of the normal cervical lordosis, keeping the chin tucked. Abnormal movement is compensated by the tightness of the SCM, producing an early protraction of the chin directly upward at the beginning of the motion [8].

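### Scapular dyskinesis is a yes/no outcome, but the analysis section summarises all variables as mean and SD and names only methods for means

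*Protocol article*

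**What the plan says.** The section Outcome measures names upper trapezius activation as primary. Its secondary outcomes are the other EMG measurements together with "scapular dyskinesis, forward head and shoulder angles, thoracic kyphosis angle, and neck flexion pattern".

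Two of these are not described on a continuous scale:
- **Scapular dyskinesis.** Position and motion are "characterized by dyskinesis as a “yes” (presence of deviation or dysrhythmia/asymmetry bilaterally) or “no” (no presence").
- **Neck flexion pattern.** The test section describes two kinds of movement and prints no score: "Normal movement produces a smooth reversal of the normal cervical lordosis, keeping the chin tucked", and "Abnormal movement is compensated by the tightness of the SCM", with early protraction of the chin.

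Dyskinesis is also used to select participants. Under Study participants and eligibility criteria, "participants who have any abnormality in the position and rhythm of the scapula, as measured by the scapular dyskinesis test, will be recruited".

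The section Statistical method and analysis then says that "All variables will be reported using the descriptive statistic (mean, standard deviation"). It adds a Shapiro-Wilk check, states that "Repeated measures ANOVA will be used to compare the means", and provides for Bonferroni-adjusted post-hoc tests, independent t-tests between groups and an effect size by the Cohen method. It mentions no counts or percentages, no categorical test, and no alternative if normality fails.

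**The concern.** The summary prescribed for every variable does not fit an outcome that the same article defines as yes/no. This is a stated choice, not merely an omission, so a later analysis plan would have to overrule the sentence rather than fill a gap.

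The study objectives name movement patterns (scapulohumeral rhythm and neck flexion) as one of three components of the primary aim, and these two tests are the listed outcomes that address them. Three things are at stake:
- A mean, SD and Cohen's d for a 0/1 variable that starts at or near a constant are hard to interpret.
- With about 9 to 12 men per arm, the choice between a t-test and an exact test can decide whether a small difference is called significant.
- Because participants are selected for a positive test, a fall in dyskinesis within an arm can arise partly from selection and retest error.

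**Working it through.** **Inputs.** The Sample size section gives a minimum of 18 and a planned enrolment of 24. At 1:1 allocation (Randomization section) that is 9 or 12 per arm. Alpha is 0.05, taken as two-sided because the article does not say. Assessments are at baseline, 8 and 12 weeks. The article prints no figure for the dyskinesis analysis, so there is none to reproduce.

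**1. Baseline.** If the screening result is the baseline value, everyone is coded 1. With 12 men in each arm, SD = 0, and a baseline t statistic is 0/0, which is undefined. If dyskinesis is re-scored at a separate baseline visit, some men may score no, and the variance is small rather than zero.

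**2. Normality.** Shapiro-Wilk was applied to every non-constant 0/1 sample of 12. The largest p-value, at 6 ones and 6 zeros, is 0.0003. The plan's own check therefore fails whenever the outcome varies at all, and no alternative is named.

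**3. Planned t-test against Fisher's exact test.** Suppose no control changes from yes to no, and k of n men in the intervention arm do.

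- Pooled t-test: the arm variances are n·p·(1−p)/(n−1) with p = k/n, and 0. The pooled variance s² is half the former, and t = p / √(2s²/n) on 2n−2 degrees of freedom.
- Fisher two-sided, for these tables: p = 2·C(n,k)/C(2n,k).

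For n = 9, k = 4:
- The intervention-arm variance is 9 × (4/9) × (5/9) / 8 = 0.278, so s² = 0.139.
- t = 0.444 / √(2 × 0.139/9) = 2.53 on 16 df, p = 0.022.
- Fisher: 2 × 126/3060 = 0.082.

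For n = 12, k = 4:
- The intervention-arm variance is 12 × (1/3) × (2/3) / 11 = 0.242, so s² = 0.121.
- t = 0.333 / √(2 × 0.121/12) = 2.35 on 22 df, p = 0.028.
- Fisher: 2 × 495/10626 = 0.093.

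| Per arm | Changes, control vs intervention | t-test p | Fisher p |
|---|---|---|---|
| 9 | 0 vs 4 | 0.022 | 0.082 |
| 9 | 0 vs 5 | 0.006 | 0.029 |
| 12 | 0 vs 4 | 0.028 | 0.093 |
| 12 | 0 vs 5 | 0.010 | 0.037 |

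Fisher's test needs one more change than the t-test. Over all possible tables, the two disagree at 0.05 in 5 tables at 9 per arm and 8 tables at 12 per arm (counting one direction). In every one the t-test is significant and Fisher's test is not.

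**4. Type I error of the between-arm tests.** All 2×2 tables were enumerated, weighted by binomial probabilities with the same true rate of a no score in both arms. The rates are assumptions, since the article gives none.

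| True rate | t-test, 9 per arm | t-test, 12 per arm | Fisher, 9 per arm | Fisher, 12 per arm |
|---|---|---|---|---|
| 25% | 4.8% | 4.4% | 1.2% | 1.5% |
| 30% | 5.5% | 4.9% | 1.6% | 1.7% |
| 40% | 5.5% | 5.9% | 2.1% | 2.1% |
| 50% | 5.0% | 6.4% | 2.1% | 2.3% |

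At a 10% rate the t-test rejects in 0.7% (9 per arm) and 1.5% (12 per arm). It is therefore close to nominal or below it, and Fisher's test is conservative throughout.

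**The case against.** The case on the other side has four parts.

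- **The article is condensed.** The words all variables govern only the descriptive sentence. The ANOVA and t-test sentences do not list outcomes, and matching tests to outcomes is commonly left to a fuller plan. This stands in part: the article does not expressly assign ANOVA to dyskinesis. But the descriptive sentence does cover it, and no method named anywhere in the section is suited to a yes/no outcome.
- **The between-arm p-values are not badly wrong.** This stands. A reader might infer from binary data analysed as means that the randomised comparison is invalid. The enumeration does not support that: type I error is at most 6.4% in the cases computed. What remains is that the t-test is more liberal than an exact test.
- **Built-in improvement is a selection effect, not a consequence of using means.** This stands. A within-arm McNemar test would share it, and the randomised control arm deals with it in the between-arm comparison. A reader might infer a large false-positive rate by applying an unadjusted paired pre-post t-test to one arm, but the plan contains no such test: its post-hoc tests are Bonferroni-adjusted and follow a significant ANOVA. With adjustment over three visits, an arm of 9 would need 5 changes, and the chance of that with no true effect is 4.9%, 9.9% or 26.7% if 25%, 30% or 40% score no on retest. Those rates have no anchor in the article, so no size can be claimed.
- **Two premises are inferred.** This stands. No scoring rule is printed for neck flexion, and the article does not say whether the screening test also serves as the baseline value.

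**Conclusion.** The point holds, within limits. For dyskinesis, which the article defines as yes/no, mean/SD and Cohen's d are unsuitable, normality cannot hold, and baseline variance is zero or near zero by selection (exactly zero only if the screening result is the baseline value). For the between-arm comparison, the practical effect is one participant: four changes against none is significant by t-test but not by Fisher's test, at 9 and at 12 per arm. Within-arm change in dyskinesis should not be read as a treatment effect.

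For neck flexion the point is conditional on normal/abnormal scoring. The primary EMG outcome, the other EMG outcomes and the angles are continuous and unaffected. This should be fixed before analysis, but it does not undermine the trial's primary result.

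**What to change.** Revise the section Statistical method and analysis as follows:
- Report scapular dyskinesis as n (%) per arm and visit.
- Compare the proportion without dyskinesis between arms at weeks 8 and 12 by Fisher's exact test, with an exact or score-based 95% confidence interval for the risk difference. Base conclusions on this between-arm comparison, not on change within an arm.
- State how neck flexion is scored. If it is normal/abnormal, make the same comparison stratified by baseline result.
- Limit mean/SD, ANOVA and Cohen's d to the EMG and angle outcomes.

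The cost is a few lines of text and no extra data. The article's Trial status section reports recruitment still under way, so the change could be made before analysis. The downside is that Fisher's test is conservative at this size, so significance on these outcomes becomes slightly harder to reach.

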## Discussion

We propose to evaluate the effectiveness of a randomized controlled trial of a CCEP in a group of men aged 18 to 28 years with UCS in terms of their alignment, selected muscle activation, and relevant movement patterns.

Clinicians believe that it is important to quantify head, shoulder, scapulae, and spinal posture behavior as they influence and are influenced by many biomechanical, motor control, and performance variables [43]. It has been assumed that exercise can correct postural malalignment, but an earlier review found little evidence to support this assumption [17]. Moreover, despite the widespread inclusion of postural correction in exercise interventions, there are limited empirical data to support its effectiveness and little is known about the most effective exercise interventions [24]. As already mentioned, it seems the most important reason is the adherence to the traditional structural approach in the previous studies. We want to conduct a randomized controlled trial based on the comprehensive approach which is adequately powered and utilizes validated outcome measurements of UCS to investigate the effects of the CCEP on both our primary and secondary outcomes. If the CCEP results in changing the alignment, muscle activation, and movement pattern, or all three, we will examine the pathways of change to determine whether changes in the alignment, muscle activation, or movement pattern can account for the change in the UCS symptoms. Furthermore, if we find out that the CCEP can improve a postural malalignment like in UCS, this evidence could enable practitioners to recommend early intervention for UCS to prevent or delay UCS-associated consequences. Therefore, various experts in the field of corrective exercises and physical therapy, equipped with the knowledge on these changes, can identify people with UCS and also adopt appropriate therapeutic strategies to correct it and prevent the occurrence of secondary consequences.

Our study has some limitations including the recruitment of only men 18 to 28 years of age. Therefore, the results of this study will not be generalizable to all people (e.g., women or men aged ≥ 28 years) with UCS. Another limitation is that this study is not a double-blind design since it is not possible, as is the case with most exercise trials.

The results of our study will be presented at scientific conferences and published in academic journals to ensure that our study will inform therapists in practice and prove beneficial to patient care. Our goal is to conduct a clinical trial that will provide therapists with evidence of the efficacy of the CCEP on the keystone and the side effects of UCS. Previous trials have often used only assessment of the alignment to investigate the improvement of a malalignment. However, we are focusing on alignment, muscle activation, and movement pattern simultaneously based on the comprehensive approach. Therefore, if our exercise intervention proves successful, our approach to improving UCS could represent a fundamental paradigm shift in exercise intervention strategies to improve postural malalignments and their consequences. Results from our trial may provide new insights into the effects of exercise not only on alignment but also on muscle activation and movement pattern, which are important outcomes for people with postural malalignments and, if successful, it could assist practitioners in individualized clinical decision-making. However, our results may have a limited transferability to all people and thus may be valid only for men.

### Trial status

This trial was registered on 2018-10-26 (registration number IRCT20181004041232N1, protocol version number 34266, https://en.irct.ir/user/trial/34266/view). The trial is currently in the stage of recruiting patients. The first patient was included on 2019-02-01. To date, ten patients have been included. The recruitment will be completed on approximately 2019-07-01.

## Data Availability

The authors aim to make the datasets supporting the results and conclusions of this study available as supplementary files in future published articles.

## Appendix 1

### Comprehensive corrective exercise program

The duration of the exercise protocol is 8 weeks, with three sessions per week, and each session will be about an hour. Each exercise session begins with 10 min of warm-up activity and ends with 5 min of cool-down. Selected exercises are designed in three phases: initial, improvement, and maintenance [35].

#### Initial phase exercises

The initial phase exercises (Fig. 3) include laying supine on a foam roll in three different arm abduction angles (exercise 1A–C), side-lying external rotation (exercise 2), side-lying forward flexion (exercise 3), standing diagonal flexion (exercise 4), and military press (exercise 5). Participants with less ability can do exercises 4 and 5 in a sitting position. Once a participant regains muscle balance in the static conditions, he will try to add upper extremity movements in exercise positions. Exercises progress in frequency and intensity during this phase, as long as participants are able to demonstrate good quality movement. The initial phase duration is 2 weeks and the exercises will be performed for seven sets of 10-s hold to ten sets of 15-s hold.

#### Improvement phase exercises

The goal of the improvement phase is to create the necessary tissue adaptations in the participant. Therefore, during this phase Thera-Bands, weights, and training balls will be used. Improvement phase exercises (Fig. 4) include side-lying external rotation with a dumbbell (exercise 6), side-lying forward flexion with a dumbbell (exercise 7), standing diagonal flexion with a dumbbell (exercise 8), standing external rotation with Thera-band (exercise 9), standing diagonal flexion with Thera-band (exercise 10), abduction in sitting on a training ball (exercise 11), lying prone V, T, and W exercises (exercise 12), and abduction in standing on a balance board (exercise 13). Exercises are progressed by considering individual characteristics of each participant and by observing the overload principle and the progression in the number of repetitions of each set during the 4 weeks of the improvement phase. The exercises will be performed from five sets of ten repetitions to six sets of 15 repetitions.

***Maintenance phase exercises:*** The exercises are the same as in the improvement phase without any progression in intensity and frequency. The maintenance phase duration is 2 weeks.

## Appendix 2

**Table 2 Tab2:** The locations of electrodes and MVIC positions

Muscle	Electrode location	MVIC position
Upper trapezius	The halfway point between the spinous process of the seventh cervical vertebra and the acromion	In a sitting position with abduction at 90°
Middle trapezius	The halfway point between the scapular medial border and the T3	In a prone position with horizontal abduction at 90° and external rotation
Lower trapezius	At 2/3 on the line from the trigonum spinea to the T8	In a prone position with horizontal abduction in 120° in line with the fibers of the muscle and the thumb pointing upward
Serratus anterior	In the mid-axillary line over the fifth rib	In a sitting position with maximum resistance given to upward rotation of the scapula with the shoulder flexed
Middle deltoid	The halfway point of the acromion and the deltoid tuberosity	In a sitting position with abduction at 90°
